Many services that were previously only provided face-to-face or through outpatient services have successfully, after the COVID-19 pandemic, transitioned to a telehealth service [21]. Still, issues with telehealth delivery persist, including device and internet capabilities at the end of the consumer, the unfamiliarity of the user interface, and uncertainty regarding the cost-effectiveness at the end of the provider [21,22].

Although intensive interventions, including multidisciplinary care and home visits, have been shown to reduce short-term readmissions, they may not be cost-effective in all settings and are difficult to implement across an organization. Low-intensity interventions, such as phone calls, are easy to implement; however, they have not been shown to impact readmission rates by themselves [23]. What is needed is a low-cost intervention that combines multiple interventions into a coordinated package, which can be delivered without requiring face-to-face or outpatient consultations and which, if successful, can be readily spread across an organization.

The transitional care model (TCM) is a nurse-led multidisciplinary model of care developed at the University of Pennsylvania [24]. It focuses on improving the transition of older adults with complex health needs from hospital to home, aiming to reduce hospital readmissions, improve overall patient outcomes, and demonstrate lower overall health care costs by providing comprehensive coordinated care during the critical period following hospital discharge [19,25,26]. Through personalized care coordination, comprehensive assessments (including risk of readmission), ongoing time-limited follow-up, nursing care, and interventions, the TCM has proven effective in enhancing patient care quality while lowering health care costs [26].

To date, there is no evidence that the TCM has been implemented or adapted for implementation within the Australian health care system. However, related transitional care interventions have been trialed. An umbrella review by Berthelsen et al [27], which synthesized findings from 59 randomized controlled trials and 3 quasi-experimental studies relating to key components of the TCM, included 5 systematic reviews conducted in Australia. In these reviews, 5 Australian studies were identified. However, these studies were not direct implementations of the TCM.

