**Secondary**					
	**Health care use**				
		The rate of hospital re-presentation within 1, 6, and 12 months of discharge from the index admission	Readmission data available from electronic medical record Rate defined as the number of re-presentations over a unit of time (eg, 1 y) Statistical analysis: nonparametric comparison of rates of re-presentation between treatment and control groups		
		Overall length of hospital stay within 1, 3, 6, and 12 months of discharge from the index admission	Readmission data available from electronic medical record Defined as the cumulative number of days spent in hospital over a unit of time (eg, d/y) Statistical analysis: nonparametric comparison of rates of re-presentation between treatment and control groups		
		Cost of transition service	Economic benefits of the intervention will be confirmed through a comparison of subsequent rehospitalization costs in the treatment and control groups		

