	**Organization of care**				
		Implementation of components of the TCM^d^	Economic benefits: cost calculations of comparison between control and intervention hospital readmissions from the index admission Includes TCM intervention cost compared with usual care cost		
		Implementation of the transition action plan for all patients	Customized transition action plan developed		

^a^ESAS: Edmonton Symptom Assessment System.

^b^GSE: General Self-Efficacy Scale.

^c^PCCQ: Patient Continuity of Care Questionnaire.

^d^TCM: transitional care model.

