### Sample Size Estimation and Justification

We anticipate that the enrollment of approximately 200 patients over 15 months will be feasible and provide a sufficient sample size to achieve the primary outcome, with the anticipated baseline readmission rate in the control group and absolute reduction in the intervention group (Table 3). Enrollment commenced in February 2024 and was completed on March 31, 2025. Given that the primary end point will be derived from health information systems in South Australia and that the study has an intention-to-treat approach, there will be a need to consider a larger sample size, taking into account withdrawals, dropouts, or loss to follow-ups.

**Table 3 table3:** Sample size per group by baseline readmission rate and absolute reduction in readmission with 80% power (α=.05).

Absolute reduction in readmission rate in the intervention group (%)	Baseline readmission rate in the control group at 3 mo, n		
	35%	40%	45%
15	136	150	160
20	70	79	86
25	40	47	52

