## Discussion

### Anticipated Findings

The primary outcome of this research is decreasing the rate of hospital readmission within 3 months of discharge from the index admission in people with multimorbidity. In a prospective, quasi-experimental TCM study (N=172), improvements in all health status and quality of life measures were observed after intervention compared to before the intervention, and a significant decrease in total number of readmissions (TCM: 45 readmissions vs control: 60 readmissions; *P*<.041) and total hospital days (TCM: 252 d vs control: 351 d; *P*<.032) were observed at 3 months [57].

The secondary outcomes include the cost analysis of the transition service model of care. In a previous study, cost savings were demonstrated in relation to appropriate implementation of the TCM, whereby it was associated with a short-term decrease of US $439 per patient per month in total health care costs at 3 months and cumulative per-patient savings of US $2170 at 1 year (*P*<.037). In a cost comparison study in which the post–acute care costs of 3 care management interventions for hospitalized older adults with cognitive impairment and their family caregivers were compared (N202), the TCM had significantly lower costs than 2 other comparable care management interventions and has been associated with an estimated net savings of US $2972 per individual at 6 months [26].

People with multimorbidity are readmitted to the hospital more, spend more time seeking health care, and often receive fragmented care. When they are discharged from the hospital, they are often readmitted due to poor health care team communication, uncoordinated follow-ups, and not knowing whom to contact when they have symptoms. Supporting these patients as they transition to the community after hospital discharge with an adapted nurse-led TCM intervention will assist them to resume their normal lives more quickly and prevent unnecessary hospital contact.

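### Table 2 defines economic benefit in two inconsistent ways, and the definition under the designated cost outcome leaves out the cost of delivering the service

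*Protocol article*

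**What the plan says.** Table 2 (Statistical Analysis section) deals with cost in two places.

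- **Health care use.** The outcome is labelled "Cost of transition service". Its entry reads: "Economic benefits of the intervention will be confirmed through a comparison of subsequent rehospitalization costs in the treatment and control groups". No other cost is named.
- **Organization of care.** Under the outcome on implementing the components of the transitional care model (TCM), the entry reads: "Economic benefits: cost calculations of comparison between control and intervention hospital readmissions from the index admission". It then adds: "Includes TCM intervention cost compared with usual care cost".

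The Aim and Objectives section lists a cost analysis without naming its components. The Discussion (Anticipated Findings) is equally general: "The secondary outcomes include the cost analysis of the transition service model of care". Neither says which Table 2 row decides whether the service is of economic benefit.

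**The concern.** The row named for the cost of the service does not measure that cost. It also does more than list a quantity to be reported, because it states how economic benefit will be confirmed, and the quantity it uses is a gross hospital saving.

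The omitted cost arises in the intervention arm. According to the Intervention section, those participants receive a transition action plan, a contact in the first 48 hours after discharge, weekly and then fortnightly contacts, a multidisciplinary case discussion and a final nurse consultation. The Control section says that the nurses do not follow up services for controls. A comparison of hospital costs alone therefore credits the intervention with any saving and does not charge it for delivery.

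This matters for what the trial sets out to show. The Background justifies the design on cost: "What is needed is a low-cost intervention that combines multiple interventions into a coordinated package". The Discussion introduces the cost outcome with earlier findings expressed as total health care costs and as net savings, and a rehospitalization-only figure is not comparable with either. The Limitations section places the trial in a programme to make the model standard care, so the economic result may well inform adoption.

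**Working it through.** The plan states no cost figure for this trial, so there is none to reproduce. The check compares the two rows and then uses simple algebra.

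**1. The rows side by side**

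| | Health care use row | Organization of care row |
|---|---|---|
| Outcome label | Cost of the service | Implementation of TCM components |
| Hospital readmission cost compared between arms | Yes | Yes |
| Intervention cost | Not named | Included |
| Usual-care cost | Not named | Included as comparator |
| Tied to a statement of economic benefit | Yes, as the means of confirming it | Yes |

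The rows share the hospital component. The second adds a component that the first leaves out.

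**2. What each row computes.** Per randomised patient, let

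- G = mean rehospitalization cost in controls minus that in the intervention arm;
- S = incremental service cost, that is, the delivery cost of the intervention plus any difference between arms in usual-care follow-up cost.

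The first row gives G. The second, read as a net comparison, gives N = G − S. Hence G − N = S, so the first row differs from the net result by exactly S. For S > 0 the two have opposite signs when 0 < G < S.

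**3. Illustration with assumed unit costs.** Let d be the absolute reduction in the readmission rate and C the cost of a readmission. If each patient kept out of hospital avoids one readmission, G = d × C. Table 3 (column heading "Absolute reduction in readmission rate in the intervention group") supplies d = 0.15, 0.20 and 0.25. The documents give neither C nor S. The assumed ranges are C = 2,000 to 20,000 and S = 500 to 3,000 currency units.

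Break-even service cost (d × C), above which a gross saving becomes a net loss:

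| d | C = 2,000 | C = 5,000 | C = 10,000 | C = 20,000 |
|---|---|---|---|---|
| 0.15 | 300 | 750 | 1,500 | 3,000 |
| 0.20 | 400 | 1,000 | 2,000 | 4,000 |
| 0.25 | 500 | 1,250 | 2,500 | 5,000 |

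Two cases at d = 0.20:

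- C = 5,000: G = 0.20 × 5,000 = 1,000, a benefit under the first row. N = 1,000 − 500 = +500 at S = 500; 1,000 − 1,500 = −500 at S = 1,500; 1,000 − 3,000 = −2,000 at S = 3,000.
- C = 20,000: G = 4,000. N = +3,500, +2,500 and +1,000 at the same three values of S, so the sign never changes.

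The two rows can therefore lead to opposite conclusions or to the same one, depending on inputs that the documents do not contain. A true reduction below 15 points would lower the break-even cost in proportion.

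**The case against.** The strongest reply is that the plan as a whole does cost the service. The Organization of care row commits to the intervention cost set against usual care, and if both rows are reported a net loss would be visible. This stands. A reader might infer from the first row that the service cost is left out of the trial, but the same table shows otherwise.

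A reader might also infer that the two rows say opposite things. The text does not support that. Both compare readmission costs; one adds the service cost, and the other omits it without expressly excluding it. A compatible reading is possible, in which the label supplies the service cost and the entry supplies the hospital cost to set against it. But the entry does not say so. It names one comparison and says that this comparison will confirm benefit.

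A third reply is that a condensed article may leave cost components and perspective to a fuller document. That is fair for missing detail, and none is claimed here. The point is that two stated definitions disagree, and an analysis plan written from Table 2 would inherit both.

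Finally, no sign reversal has been shown for this trial. That is correct. The illustration shows only that a reversal is possible.

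**Conclusion.** The inconsistency is real and should be corrected. Economic benefit has two definitions, and the one attached to the designated cost outcome would, as written, show a benefit whenever rehospitalization costs fall, whatever the service costs. A misleading conclusion follows only if that row is applied on its own.

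The overstatement is S per patient, the incremental service cost. No monetary size or likely direction of the net result should be attached to this, because the documents give neither the delivery cost nor the cost of a readmission. The claim that the first row is the more favourable one assumes S > 0, that is, delivery cost is not fully offset by lower usual-care follow-up cost in the intervention arm.

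The problem is confined to one secondary outcome. The primary outcome, its analysis and the sample size are untouched.

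**What to change.** Align the two rows of Table 2, and carry the wording into the analysis plan before costs are compared by arm:

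- Define the cost outcome in the Health care use row as the between-arm difference in net cost per randomised patient: intervention delivery cost and usual-care follow-up cost, each as incurred in each arm, plus subsequent hospital cost.
- Keep the usual-care comparison that the Organization of care row promises, and have that row refer to the same definition. Deleting that row, or setting follow-up cost in controls to zero, would lose this comparison.
- Report rehospitalization cost by arm as a component, and state that it does not by itself confirm economic benefit.

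The cost is a wording change. The Organization of care row already commits to obtaining the intervention and usual-care costs, so no new kind of data is requested. The downside for the sponsor is that the reported saving becomes less favourable than the gross hospital figure.

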	**Model of care and patient outcomes**				
		Patient-reported symptom burden	ESAS^a^ [52] (nonparametric comparison of responses between treatment and control groups)		
		Patient symptom management and self-efficacy	ESAS [52] GSE^b^ [51] (nonparametric comparison of responses between treatment and control groups)		
		Quality of life	EQ-5D-3L health questionnaire [44]		
		Patient experience, satisfaction, and perceived continuity of care	PCCQ^c^ (short) [45] (nonparametric comparison of responses between treatment and control groups)		

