**Objective:**

This study aims to assess the impact of a TCM on 3-month readmission rates in people with multimorbidity after discharge in an Australian context. Other objectives include evaluating the rate of re-presentation to hospital and overall length of hospital stay within 1, 6, and 12 months of discharge from the index admission; conducting a cost analysis of the transitional service model of care; evaluating the patient experience with the transition service; assessing patients’ symptom burden before and after transitional support service intervention; and evaluating patients’ quality of life, self-efficacy, and symptom management before and after intervention.

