### Statistical Analysis

An intention-to-treat approach will be used. Linear regression analyses will be conducted to estimate the effects of the intervention on primary and secondary outcomes. A fixed effects model will be used to account for stratification at the hospital and unit levels. Sensitivity analyses will be performed to assess the robustness of the findings. Table 2 presents the alignment of data analysis with primary and secondary study outcomes.

**Table 2 table2:** Primary and secondary outcomes—measurement and statistical analysis.

Outcome					Data source, measurement, and analysis

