### Intervention

The intervention involves establishing a transition coordination service led by nursing transition coordinators, who will support transitions and referrals, known as STARnurses. The intervention consists of 4 key phases.

The first phase involves in-hospital screening in which “risk of readmission” screening is conducted during the hospital stay, using the Community Assessment Risk Screen tool [41,42]. Patients who meet the inclusion criteria are invited to participate in the study.

The second phase involves in-hospital baseline assessment, transition planning, and participant goal setting (following participant research and information discussion, acceptance to participate, and consent procedure complete). A detailed inpatient baseline and transition assessment is performed to collaboratively develop personalized goals and a transition action plan. Researchers will use the following tools to assess participants’ transition needs: customized transition nursing assessment [43], Barthel Index [46], Edmonton Frailty Scale [47,48], Kessler Psychological Distress Scale [49], Malnutrition Universal Screening Tool scale [50], and General Self-Efficacy Scale [51]. The participant’s GP or practice nurse will be contacted and receive the transition action plan before the participant’s hospital discharge.

The third phase is posthospital discharge transition coordination. Participants will receive transitional care coordination, with phone calls or telehealth follow-up in the first 48 hours following discharge and then weekly and fortnightly (Figure 1).

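### For the symptom and self-efficacy scores (ESAS, GSE) the article names two different analyses, and neither names the baseline score that would sharpen the comparison

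*Protocol article*

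**What the plan says.** - **Table 2, Model of care and patient outcomes.** The ESAS, GSE and PCCQ rows carry the same analysis: "nonparametric comparison of responses between treatment and control groups". No time point, change score or baseline term is given. The EQ-5D-3L row names the instrument and no analysis.
- **Statistical Analysis.** "Linear regression analyses will be conducted to estimate the effects of the intervention on primary and secondary outcomes". The only model terms named are the stratification factors: "A fixed effects model will be used to account for stratification at the hospital and unit levels". The same section presents Table 2 as the outcome-by-outcome version of this plan.
- **Abstract, Objective.** The stated aims include "assessing patients’ symptom burden before and after transitional support service intervention" and "evaluating patients’ quality of life, self-efficacy, and symptom management before and after intervention". Patient experience is listed without a before-and-after description.
- **Intervention, second phase.** The in-hospital baseline tools end with "Malnutrition Universal Screening Tool scale [50], and General Self-Efficacy Scale [51". ESAS, EQ-5D-3L and PCCQ are not in that list. Figure 1, which sets out the data collection time points, is not shown.

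**The concern.** Two methods are stated for the same secondary outcomes, and they answer different questions. A rank comparison tests whether scores tend to be higher in one arm. A linear regression estimates a mean difference, here within hospital and unit. With both in print, the choice between them could be made after the results are known.

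Neither statement names the participant's own starting score, although for GSE that score is collected and for ESAS the abstract implies it. Baseline is usually the strongest predictor of a later patient-reported score. Leaving it out keeps avoidable noise, and any chance baseline imbalance, in the comparison. The sample of about 200 was chosen for re-presentation to hospital. No patient-reported outcome has a power calculation, so precision on these scores is not protected elsewhere in the plan.

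**Working it through.** **The plan's own figure.** The only sample size figures are in Table 3, for the primary binary outcome. They follow from n = (1.960 + 0.842)² × [p1(1−p1) + p2(1−p2)] / d². For 35% against 20%: 7.849 × (0.2275 + 0.1600) / 0.0225 = 135.2, so 136, as printed. All nine cells match. This fixes the conventions used below (two-sided 5%, 80% power) but says nothing about the patient-reported scores.

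**Inputs.** About 200 patients (Sample Size Estimation) at 1:1 (Randomization) gives 100 per arm. Assumptions not in the documents: baseline-to-follow-up correlation r of 0.3 to 0.7, a true difference of 0.4 SD, normally distributed scores and no attrition.

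**Formulas.**
- ANCOVA multiplies the variance of a follow-up-score comparison by 1 − r².
- The equivalent sample per arm without adjustment is 100 / (1 − r²).
- The detectable difference at 80% power without baseline is 2.802 × √(2/100) = 0.396 SD for a comparison of means. For the rank test (relative efficiency 0.955) it is 2.802 × √(2/95.5) = 0.405 SD.
- With baseline, the detectable difference is 0.396 × √(1 − r²).

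| r | 1 − r² | Variance cut | Equivalent n per arm | Detectable difference, ANCOVA | Power at 0.4 SD, ANCOVA |
|---|---|---|---|---|---|
| 0.3 | 0.91 | 9% | 110 | 0.378 SD | 0.843 |
| 0.5 | 0.75 | 25% | 133 | 0.343 SD | 0.904 |
| 0.7 | 0.51 | 49% | 196 | 0.283 SD | 0.977 |

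Without baseline, power at 0.4 SD is 0.789 for the rank test and 0.807 for a comparison of means. The gain from adjustment is therefore about 5, 12 and 19 points over the rank test, or 4, 10 and 17 points over a regression that omits baseline.

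**Check by simulation** (4,000 trials per setting, 100 per arm, 0.4 SD):

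| r | Rank test, follow-up | Rank test, change | ANCOVA | Rank ANCOVA |
|---|---|---|---|---|
| 0.3 | 0.806 | 0.651 | 0.854 | 0.832 |
| 0.5 | 0.791 | 0.794 | 0.902 | 0.881 |
| 0.7 | 0.783 | 0.943 | 0.976 | 0.960 |

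The gain of ANCOVA over the rank test of follow-up scores is again about 5, 11 and 19 points. If the responses in Table 2 are meant as change scores, the rank test still falls below ANCOVA at every r, and at r = 0.3 it does worse than ignoring baseline. With no true difference, every method rejected in about 4% to 5% of trials.

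**The case against.** The best defence is that the article condenses a fuller plan. Covariates, time points and the form of the score commonly sit in an analysis plan that is not shown, and silence on them is no fault. That stands, and it limits the point. It does not excuse the article for naming two different methods for the same outcomes.

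Several stronger readings are tempting, and the text does not support them:

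- A reader might infer that baseline is discarded for all patient-reported outcomes. Table 2 does not say whether responses are follow-up or change scores, EQ-5D-3L has no stated method, PCCQ has no stated baseline, and only GSE is in the listed baseline assessment.
- A reader might infer a within-group before-and-after test that would credit natural recovery to the service. Table 2 specifies a comparison between arms for ESAS, GSE and PCCQ, and the objectives in the main text do not use the before-and-after wording. No within-group test is planned.
- A reader might infer that no effect size will be reported. The regression in the Statistical Analysis section would give one.
- A reader might take the result to be biased. Randomisation protects the comparison, and the simulated type I error is unaffected.

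It is also fair that a rank test is a defensible choice for bounded scores such as the 0 to 10 ESAS ratings, and that the gain is small if r is low.

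**Conclusion.** The point holds as an inconsistency with a cost in precision, for ESAS and GSE. Two sections name different methods for the same secondary outcomes, and neither names the baseline score. The likely loss is about 5 points of power at r = 0.3 and 19 at r = 0.7 relative to a rank test of follow-up scores, at 0.4 SD with 100 per arm. In detectable difference, that is 0.405 SD against 0.378 to 0.283 SD. The correlation, effect size, normality and full follow-up are assumptions, so the range is indicative. The validity of the comparison and the primary outcome are not in question. The issue is worth correcting because the correction is nearly free, but it does not threaten the trial.

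**What to change.** Make the Statistical Analysis section and Table 2 name the same primary method for these outcomes: the between-arm difference at a stated follow-up time, from ANCOVA or a mixed model over time points, adjusted for the baseline score and the randomisation stratum, with a 95% confidence interval. If scores are markedly skewed, use rank ANCOVA or ordinal regression. Keep the rank test as a sensitivity analysis.

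Apply this to GSE, and to ESAS and EQ-5D-3L where baseline is recorded in both arms. The EQ-5D-3L row then also gains a stated analysis. Keep the between-group rank comparison for PCCQ if it is measured only after discharge.

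The cost is wording and a little analysis work, with no new data, provided controls have baseline scores. A comparison of follow-up scores alone would not need them, so their existence cannot be taken from Table 2. The baseline assessment is described under Intervention, and the Control section does not mention it, so this must be confirmed first. Data collection is reported as complete, so the choice should be recorded and dated before any results by arm are examined.
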